### Study population

Eligible patients are adults (≥18 years) hospitalized in study ICUs with AKI compatible with the diagnosis of acute tubular necrosis in a context of ischemic or toxic aggression and receiving invasive mechanical ventilation or catecholamine infusion. To be randomized, patients must fulfill at least one of the three following criteria: serum creatinine concentration > 354 μmol/l or greater than three times the baseline creatinine level, anuria (urine output <100 ml) for more than 12 hours, oliguria (urine output <0.3 ml/kg/h or <500 ml/day) for more than 24 hours. These three criteria represent stage 3 of the KDIGO classification [20].

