### Data collection and follow-up

#### At day zero (D0)

Demographic data and medical history, including the current clinical history with the reason for ICU admission, Simplified Acute Physiology Score III and Sequential Organ Failure Assessment score will be collected. Potential exposure to nephrotoxic agents (for example, aminoglycosides or contrast agents) will be documented. Details of treatments including mechanical ventilation (and its settings), fluid therapy, catecholamine and anticoagulant administration are recorded.

Laboratory tests include determination of serum (and urine if diuresis is present) electrolyte levels, serum glucose level, urea and creatinine concentration, arterial blood gas content, and liver and muscle enzyme concentrations. No renal failure marker identification (such as neutrophil gelatinase-associated lipocalin) is planned because the clinical usefulness of these markers in routine care has not yet been demonstrated [19].

Baseline (that is, before occurrence of AKI) serum creatinine concentration will be recorded. Baseline serum creatinine concentration will be determined from either the results of a measurement in the 12 months preceding the ICU stay or estimated using the Modification of Diet in Renal Disease Study Group formula [22]. As a special case, if serum creatinine concentration was measured more than 12 months before admission, the baseline level will be considered as the higher of the two estimates (former serum concentration or that computed using the Modification of Diet in Renal Disease formula).

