#### Secondary endpoints

Secondary endpoint measures are the percentage of patients receiving RRT at least once in the ‘delayed’ RRT strategy arm (compared with the 100% of patients in the ‘early’ strategy); the number of RRT sessions per patient (analyzing living and dead patients separately); the time between randomization (D0) and RRT initiation; the time between observation of at least one of the severity criteria (which mandates RRT in the delayed strategy) and RRT; the time to RRT weaning; the number of days alive without RRT (between D0 and up to D28); the time between D0 and the first RRT and between the last RRT and D60; the number of dialysis catheter-free days between D0 and D28; the rate of adverse events potentially related to AKI or RRT (including: (a) hemorrhage requiring red blood cell transfusion or surgical procedure, (b) thrombocytopenia (<100,000 platelets/mm^3^), (c) thrombosis of a large venous axis diagnosed by Doppler ultrasonography, (d) hypokalemia (defined as serum potassium concentration < 3 mmol/l), (e) hypophosphatemia (defined as a serum phosphate concentration < 0.6 mmol/l), (f) hyperkalemia (>6.5 mmol/l), (g) cardiac rhythm disorders (ventricular tachycardia, ventricular fibrillation, torsades de pointes or a new episode of atrial fibrillation requiring medical treatment or external electric counter shock); the number of days alive without mechanical ventilation between D0 and D28; the rate of nosocomial infections (bloodstream, lung and catheters and unexplained bacteremia or fungemia); the number of days alive without vasopressors between D0 and D28; the progression of organ failures assessed using the Sequential Organ Failure Assessment score; the duration of stay in the ICU and in hospital generally (limited to D60); the survival rate at D28; the proportion of patients with treatment limitations (withholding or withdrawal); and the total cost of RRT-related consumables between D0 and D28 (catheters, solutions for RRT, membranes, and circuitry).

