#### Other analyses

Categorical variables will be compared using the χ^2^ or Fisher’s test, as appropriate. Continuous variables will be compared using Student’s *t* test or the Wilcoxon test, as appropriate.

The analysis of the overall survival will be adjusted for important stratification and prognostic factors using a multivariate analysis (Cox model). The adjustment factors will include: baseline Simplified Acute Physiology Score III, RRT technique used, treatment with catecholamines at baseline, mechanical ventilation at baseline, septic shock at baseline, time between admission in ICU and AKI development (less than, greater than, or equal to 7 days).

All secondary analyses will be conducted at the bilateral alpha risk of 5%.

Analyses will be performed using R software (R Foundation for Statistical Computing, Vienna, Austria) version 2.14 or later, or SAS version 9.2.

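### Ventilator-free and vasopressor-free days are compared without adjusting for support at D0: the tests are valid but give up precision that is free to recover

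*Protocol article*

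**What the plan says.** The protocol article's Secondary endpoints section lists "the number of days alive without mechanical ventilation between D0 and D28" and "the number of days alive without vasopressors between D0 and D28".

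Under Study population, eligibility includes "receiving invasive mechanical ventilation or catecholamine infusion". Either support is enough, so a patient can enter without the other.

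The D0 data collection section states: "Details of treatments including mechanical ventilation (and its settings), fluid therapy, catecholamine and anticoagulant administration are recorded". Table 1 marks mechanical ventilation and catecholamine treatment at inclusion.

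The Randomization section names centre as the only stratification factor.

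For the test, Other analyses states: "Continuous variables will be compared using Student’s *t* test or the Wilcoxon test, as appropriate". Covariate adjustment appears in that section for survival only: "The analysis of the overall survival will be adjusted for important stratification and prognostic factors using a multivariate analysis (Cox model". Its listed factors include "treatment with catecholamines at baseline, mechanical ventilation at baseline, septic shock at baseline".

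**The concern.** For a patient ventilated at D0, the count of ventilator-free days mainly reflects how soon ventilation ends. For a patient not ventilated at D0, it mainly reflects whether ventilation is avoided. D0 status is therefore close to a starting value of the outcome. The same holds for catecholamines and vasopressor-free days.

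The plan treats both D0 variables as worth adjusting for in the survival model, but not for the two endpoints to which they are most directly tied. Spread between patients that comes from entry status then stays in the error term. Because nothing in the randomization balances entry status, part of that spread appears as chance differences between the arms. At stake is the precision of two of the trial's few measures of non-renal organ support.

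**Working it through.** **Inputs from the documents.** Planned enrolment is 620 (Total planned sample size), so n = 620/2 = 310 per arm. The sample size is calculated on survival alone. There is no planned figure for either support-free endpoint to reproduce, and no share on support, mean gap or SD.

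**Assumptions, for ventilation only.** Share ventilated at D0: p = 0.60 to 0.95. Mean gap in ventilator-free days between patients off and on ventilation at D0: d = 5 to 10 days, with 2 days as a low check. Overall SD: 11 days.

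**Step 1: variance explained by entry status, and its cost.** R² = p(1−p)d²/SD². The extra patients an unadjusted analysis needs for equal precision are 1/(1−R²) − 1. For example, at p = 0.60 and d = 10: R² = 0.24 × 100/121 = 0.198, and 1/0.802 − 1 = 0.247.

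| p | d = 5: R² / extra | d = 7.5: R² / extra | d = 10: R² / extra |
|---|---|---|---|
| 0.60 | 5.0% / 5.2% | 11.2% / 12.6% | 19.8% / 24.7% |
| 0.80 | 3.3% / 3.4% | 7.4% / 8.0% | 13.2% / 15.2% |
| 0.95 | 1.0% / 1.0% | 2.2% / 2.3% | 3.9% / 4.1% |

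At d = 2 the largest value, at p = 0.60, is 0.24 × 4/121 = 0.8%.

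**Step 2: the same result on the standard-error scale.** The unadjusted SE of the arm difference is √(2 × 121/310) = 0.88 day. Adjustment multiplies it by √(1−R²). At p = 0.80 and d = 7.5 it falls to 0.88 × √0.926 = 0.85 day. At p = 0.60 and d = 10 it falls to 0.88 × √0.802 = 0.79 day.

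**Step 3: chance imbalance.** The SD of the arm difference in the share ventilated at D0 is √(2p(1−p)/n). At p = 0.80 this is √(0.32/310) = 0.032, or 3.2 percentage points. The 95% range of the resulting shift is ±1.96 × SD × d. Over the grid it runs from ±0.17 day (p = 0.95, d = 5) to ±0.77 day (p = 0.60, d = 10).

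**Step 4: this is the same loss as in Step 1.** The variance of the shift divided by the variance of the unadjusted difference is [d² × 2p(1−p)/n] / [2SD²/n] = p(1−p)d²/SD² = R². At p = 0.80 and d = 10, a one-SD shift is 0.32 day, and (0.32/0.88)² = 0.13, which matches the table. The imbalance is already inside the unadjusted standard error.

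**Step 5: simulation.** This used 1,500 runs per setting, p from 0.65 to 0.93 and a gap of about 7 days.
- Type I error of the unadjusted tests was 4.4-5.9%. The simulation error is √(0.05 × 0.95/1500) = 0.6 point, so this is nominal.
- The variance ratio, unadjusted to adjusted, was 1.04-1.12.
- With true differences of about 1.9-2.4 days, adjustment raised power by 1-4 points for the t test and by 1-11 points for the Wilcoxon test.
- In the 5% of null runs with the largest imbalance in one direction (4-8 points), the unadjusted difference averaged −0.4 to −0.6 day and the adjusted one −0.15 to +0.12 day.

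**Vasopressor-free days.** The same formulas apply with catecholamine status at D0. No share or gap was assumed for that endpoint, so only the direction is claimed.

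**The case against.** The strongest objection is that nothing here is wrong. An unadjusted comparison of randomized arms is valid, and adjusting only the survival analysis is a common plan. That stands, and the simulated type I error supports it. A reader might infer that the planned tests are biased, or that imbalance shifts the result as a second harm on top of lost precision. The documents support neither: randomization makes the difference unbiased, and Step 4 shows that the imbalance and the lost precision are one quantity.

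A second objection is that covariates for individual secondary endpoints belong in the statistical analysis plan, which is not shown. This stands in part. The sentence on tests covers all continuous variables and does not rule out a supportive adjusted analysis elsewhere. But it does name a test, and the same section confines adjustment to survival. The point therefore questions a stated choice and does not ask for missing detail. If the analysis plan already adjusts these endpoints, the two texts only need aligning.

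A third objection is that the size is assumed and can easily be set too high. This also stands. With 30% off ventilation, a 12-day gap and within-group SDs of 9-10 days, one reaches about 26% of variance and 35% more patients. The plan expects mortality of 55% and 41%, on average 48%. If patients who die contribute few support-free days and mortality does not depend on entry status, a 12-day overall gap needs about 12/0.52 = 23 of the 28 days among survivors. Even a 10-day gap needs about 10/0.52 = 19. The low to middle part of the range is the safer reading.

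**Conclusion.** The point holds as a minor matter of efficiency. The planned tests of ventilator-free and vasopressor-free days are valid, but they leave out a D0 variable that is already collected and closely tied to each outcome.

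For ventilator-free days the loss is about 1-25% in patients for equal precision, more plausibly 2-13% at a 7.5-day gap. It shrinks towards nothing as the gap narrows or as nearly all patients enter ventilated. These figures rest wholly on the assumed share, gap and SD. For vasopressor-free days the direction is the same and the size is unknown.

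Both endpoints are secondary and the sample size was not set on them. Neither the trial's size nor its primary conclusion is affected.

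**What to change.** In Other analyses, add that the main comparison of ventilator-free days is adjusted for ventilation at D0, and that of vasopressor-free days for catecholamine treatment at D0. Prespecify one method for each endpoint:

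- if the Wilcoxon test would be used, a van Elteren test stratified on the D0 status;
- if the t test would be used, a linear model with arm and the D0 indicator.

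Keep the unadjusted test as a sensitivity analysis. Settle the wording before any comparison by arm is seen, so that adjustment is not a response to an observed imbalance.

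The cost is a sentence or two of analysis text. It needs no new data, visits or patients, because both variables are collected at D0 and already enter the Cox model.

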#### ‘Early’ RRT strategy

Renal replacement therapy is initiated within 6 hours after documentation of AKI stage 3 of KDIGO classification. The timing of the initiation is recorded and RRT is continued until criteria for cessation are observed.

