#### ‘Delayed’ RRT strategy

Renal replacement therapy is initiated only if one or more of the severity criteria occur. When required, RRT is performed with the same modalities and stopped according to the same criteria as for the ‘early’ RRT strategy.

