#### From D1 to D28

The same biological data as collected at inclusion will be recorded according to clinical indication for routine care until discharge from the ICU, day 28 in the ICU, or death in the ICU. A search for infection (including catheter-related infection) or complications related to RRT or AKI will be carried out according to routine care procedures. The Sequential Organ Failure Assessment score will also be calculated at D3, D7, D14, D21, and D28.

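### The SOFA organ-failure endpoint keeps its renal item, which RRT itself can change, so part of any between-arm difference can reflect allocation rather than organ function

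*Protocol article*

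**What the plan says.** The Secondary endpoints section of the protocol article includes "the progression of organ failures assessed using the Sequential Organ Failure Assessment score". The score is taken at D0, and the section on follow-up from D1 to D28 adds: "The Sequential Organ Failure Assessment score will also be calculated at D3, D7, D14, D21, and D28". Table 1 gives the same days. No section removes the renal item, names a non-renal version of the score, or says how the item is scored while a patient is on RRT.

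The arms differ in RRT exposure by design:

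- Early arm: "Renal replacement therapy is initiated within 6 hours after documentation of AKI stage 3 of KDIGO classification". The Secondary endpoints section treats this arm as fully exposed ("compared with the 100% of patients in the ‘early’ strategy").
- Delayed arm: "Renal replacement therapy is initiated only if one or more of the severity criteria occur".

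The Other analyses section provides a t test or Wilcoxon test for continuous variables, and a two-sided 5% level for all secondary analyses.

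**The concern.** SOFA is the instrument the protocol names. In its standard form it has six organ items, and the renal item is scored on creatinine and urine output. Every patient enters with stage 3 AKI, so this item is raised at baseline in both arms. RRT then removes creatinine in one arm sooner, and in more patients, than in the other.

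The endpoint should show whether the timing of RRT changes the course of organ failure. With the renal item included, total SOFA could differ between arms although native kidney function and the other five organ items are the same. If creatinine is scored as measured, the early arm may look as if it recovers faster. If patients on RRT are given the maximum renal score by convention, the early arm may look worse. Without a stated rule, a reader could not interpret even the sign of a difference.

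**Working it through.** The protocol gives no figure for the SOFA endpoint, so there is none to reproduce. The check sets its sections side by side and then illustrates the size under stated assumptions.

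**1. Timing.** Early-arm RRT starts within hours of documented stage 3, well before the first post-baseline score at D3. In the delayed arm, the criterion of prolonged oliguria or anuria needs more than 72 hours after randomization, so it cannot act before about D3. The other criteria (urea, potassium, pH, pulmonary edema) can start RRT earlier. An exposure gap at D3 is therefore expected, but its size is not given.

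**2. The protocol's own view of creatinine.** The sections on stopping and resuming RRT use a fall in creatinine as a sign of recovery only when it is spontaneous. This separates native recovery from clearance by the machine. The SOFA endpoint has no matching provision.

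**3. Measurement on the scoring day.** RRT modality, session length and interval are discretionary, and laboratory data after D0 follow routine care. The creatinine used for a score may thus depend on when the last session took place.

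**4. Shift per patient.** Assumption, not in the protocol: standard renal bands in µmol/l of 110–170 = 1, 171–299 = 2, 300–440 = 3 and >440 = 4. Study population gives the entry routes: "serum creatinine concentration > 354 μmol/l or greater than three times the baseline creatinine level", anuria, and "oliguria (urine output <0.3 ml/kg/h or <500 ml/day) for more than 24 hours".

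| Entry route | Renal item at entry | Change if creatinine is cleared and scored as measured |
|---|---|---|
| Non-oliguric, above 354 | 3 or 4 | to 2 or 1, a fall of 1 to 3 points |
| Three times baseline, e.g. baseline 70, entry just above 3 × 70 = 210 | 2 | to 2 or 1, a fall of 0 to 1 point |
| Persistent low urine output | 3 or 4, held by urine output | 0 or 1 point |

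If RRT is instead scored 4 by convention, the change runs upwards: 0 or 1 point in the first row (from 4 or 3) and 2 points in the second (from 2).

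**5. Mean shift between arms, illustration only.** Mean shift = share affected × gap in RRT exposure × shift per affected patient. Assume 50% affected, a gap of 50 to 100 percentage points, and 1 to 2 points each:

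- low: 0.5 × 0.5 × 1 = 0.25 point
- high: 0.5 × 1.0 × 2 = 1.0 point

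**6. Effect on the test, illustration only.** Suppose there is no non-renal difference. The chance of p < 0.05 in the direction of the shift is Φ(δ / (SD × √(2/n)) − 1.96), against a nominal 2.5% in that direction. Assume SD 3 to 5 and 150 to 273 evaluable patients per arm (273 is the protocol's group size for a single analysis).

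| Shift δ | Lowest (SD 5, n = 150) | Highest (SD 3, n = 273) |
|---|---|---|
| 0.25 | 6% | 16% |
| 0.5 | 14% | 50% |
| 1.0 | 41% | 97% |

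Example: δ = 0.5, SD 5, n = 150 gives 5 × √(2/150) = 0.577; 0.5/0.577 − 1.96 = −1.09; Φ = 0.137.

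The breadth of the table is the result. It shows that a modest artefact could matter, not that one of a given size will occur.

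**The case against.** The strongest reply is that the article names an instrument and assessment days and nothing more. It does not say whether the total or the components are analysed, whether change from baseline is used, or whether arms are compared at each visit. Such derivation is commonly left to an analysis plan, which is not shown and might specify a non-renal score. This stands in part: a reader might infer that the protocol fixes a comparison of total SOFA at every visit, and no section says so. Even so, the endpoint is defined by the score with no item set aside. The point is therefore about what the named endpoint measures, not about missing detail.

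The objections on size also stand. A reader might infer an artefact of 1 to 3 points in favour of the early arm. That range is per patient and applies only to non-oliguric entrants above 354 µmol/l. It does not carry over to the oliguric or three-times-baseline routes, and the mix of routes is not given. Nor can it be assumed that most delayed-arm patients are untreated at D3, since several criteria can act sooner. The document also offers no support for the idea that fluid removal by RRT changes the urine-output part of the item.

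The harm is limited too. Ventilator-free and vasopressor-free days and thrombocytopenia are separate secondary outcomes, so a reader can check a SOFA difference against them. Total SOFA can also be a fair description of a strategy's overall effect, which is a reason to keep reporting it, but not to read its renal part as organ recovery.

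**Conclusion.** The concern holds as a moderate one about a single secondary endpoint. As named, it mixes RRT exposure with organ failure through one of six items, and part of a between-arm difference in total SOFA can reflect allocation, most plausibly at early assessments such as D3.

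The document supports neither a direction nor a mean size. A reader might infer that the renal item is determined by the arm. It is not: where urine output stays low, it largely holds the score. The conclusion rests on the standard content of SOFA, which the article does not list, and on the fact that RRT clears creatinine. The primary survival analysis and the sample size are untouched.

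**What to change.** State that the between-arm SOFA comparison uses the non-renal score (the five other components) at D3, D7, D14, D21 and D28. Report total SOFA and the renal item alongside it, with one stated rule for scoring that item in patients on RRT, applied the same way in both arms.

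The cost is a sentence or two. No new data are needed, because the components are already required to compute the score. The downside is that renal function drops out of this one comparison. It remains covered by the secondary endpoints on RRT weaning and RRT-free days, and by the follow-up of dialysis dependency after D60.

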### Statistical methods

#### Sample size calculation

The aim of this study is to demonstrate a difference in outcome between two therapeutic strategies. Our primary hypothesis is that the ‘delayed’ RRT strategy might be beneficial to patients with AKI. The sample size calculation is based on the primary endpoint measure: overall survival.

The expected mortality of patients included in this type of studies may be estimated at around 55%, according to the literature [2,24-26]. Indirect evidence from retrospective studies [13,16] suggests that a 15% decrease in mortality can be expected with delayed indication for RRT (the reasons for this are explained in the discussion section).

To demonstrate a 14% decrease in mortality (from 55 to 41%, corresponding to a relative reduction in the risk of mortality by 1.5 in the ‘delayed’ RRT strategy arm, assuming exponential survival), a total of 546 subjects (273 per group) should be randomized to provide a study power of 90%, with an alpha risk of 5% between both treatments (bilateral formulation).

#### Interim analyses

Two blind and independent interim analyses (making a total of three analyses) are planned in this study. Interim analyses will be conducted after the observation of 90 and 180 deaths.

To maintain an overall type I error rate of 5%, the significance level of each analysis is adjusted, using the O’Brien & Fleming approach of group sequential analysis [27]. To maintain a power of 90%, this approach provides an increase in the planned number of subjects required for a single analysis; that is, 560 subjects instead of 546. Table 2 describes the number of events required for each analysis, the planned number of subjects and the significance levels applied for testing (with due correction).

**Table 2 Tab2:** **Number of deaths, expected number of subjects, and significance level of testing at each preplanned analysis of the primary outcome**

	**Number of deaths**	**Expected number of subjects**	**Significance level α**
Single analysis	263	546	5%
Interim analyses:			
First analysis	90	187	0.15%
Second analysis	180	373	1.81%
Final analysis	270	560^*^	4.37%

^*****^To take into account a potential loss to follow-up of about 10%, it is planned to include a total of 620 subjects in the study.

